#### **Research Plan**

Objective: To determine the effectiveness of Sani24 in the “real world” hospital environment compared to routine disinfection.

Hypothesis: Daily application of Sani24 will lead to decreased environmental bioburden compared to routine daily disinfection.

Methods:

Design: randomized controlled trial

Outcomes:

- Primary outcome – Total Colony Forming Units (CFUs) on high touch surfaces in acute care hospital rooms over a 24-hour period
- Secondary outcomes
  - o Change in CFU from baseline to 24 hours later
  - o Total CFUs of epidemiologically important vegetative bacteria (MRSA, MSSA, VRE, MDR GN)
    - Proportion of samples with epidemiologically important vegetative bacteria
  - o Change in CFU of epidemiologically important vegetative bacteria from baseline to 24 hours later
    - Change in proportion of samples with epidemiologically important vegetative bacteria
- Descriptive outcome – Patient perception of routine daily disinfection and intervention-disinfectant usage.

Approach:

- Inclusion criteria: Rooms with occupants on contact precautions
- Randomization: High touch surfaces will be randomized by right and left sides, 1:1 to intervention or control.
  - o Following collection of baseline samples:
    - Intervention – team will apply Sani24 to high touch surfaces throughout room on day 0
    - Control – no change in routine daily disinfection
- Routine disinfection tracking
  - o UV-C fluorescing gel dots will be applied to all randomized surfaces to ensure study disinfectant has not been removed from the surface
- Microbiological sampling:
  - o Location:
    - 3 samples will be obtained for each study arm, one at each point of measurement: bedrails, overbed table, and sink

- Timing:
  - Day 0 - immediately before application of disinfectant (intervention) or similar time point (control)
  - Day 1 – 24 hours following the application of disinfectant (intervention) or similar time point (control)
- Measurement:
  - CFUs on high touch objects obtained via sponge and stomacher technique
- Patients will be asked a short series of questions on day 1 about routine daily disinfection and the disinfectant if in the intervention arm
  - Question examples:
    - “How well do you think your room is cleaned?”
    - “How well do you think your room is disinfected?”
    - “Do you have any concerns about the disinfectant being used?”

Study size: 50 patient rooms will be enrolled

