- Each measured twice in three locations = 600 sponge samples

[figure not shown]

**Figure 1.** Study design.

Analysis:

Primary and secondary outcomes will be analyzed using a top-down approach.

Primary outcome – Total CFUs on high touch surfaces 24 hours after enrollment

- Total room CFU on day 1 for the entire study
- Total room CFU on day 1 compared between study arms
- Total room CFU on day 1 compared within each couplet
- Sample area CFU on day 1 for the entire study
- Sample area CFU on day 1 compared between study arms
- Sample area CFU on day 1 compared within each couplet

CFU comparisons will be analyzed using the Wilcoxon rank sum test, proportions with the proportion Z score test and categorical variables with the Chi-squared test. A p-value of 0.05 will be considered significant and all statistical tests will be 2-tailed. All testing will be completed using R software (R Foundation for Statistical Computing, Vienna, Austria).

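### The amended design matches the arms within each room, but the only test named for CFU comparisons is the rank sum test for independent samples

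*Protocol*

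**What the plan says.** All references are to the Research Plan of the Amended Protocol.

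- **Randomisation (Approach).** "High touch surfaces will be randomized by right and left sides, 1:1 to intervention or control".
- **Size and sampling.** "Study size: 50 patient rooms will be enrolled", with "3 samples will be obtained for each study arm, one at each point of measurement: bedrails, overbed table, and sink". The total is given as "Each measured twice in three locations = 600 sponge samples".
- **Listed comparisons (Analysis).** Day-1 CFU is to be summarised overall, compared between arms, and compared within pairs, at two levels: "Total room CFU on day 1 compared within each couplet" and "Sample area CFU on day 1 compared within each couplet".
- **Test (Analysis).** "CFU comparisons will be analyzed using the Wilcoxon rank sum test". The threshold follows: "A p-value of 0.05 will be considered significant and all statistical tests will be 2-tailed".

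The protocol names no signed-rank test, paired test or mixed model. It also gives no effect size, standard deviation or left-right correlation.

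**The concern.** The two sides of a room share an occupant, staff and routine cleaning, so the 50 intervention totals and 50 control totals are 50 matched pairs. A split-room design is useful because room-to-room variation drops out of the within-room difference. The rank sum test ranks all 100 totals together as if they came from unrelated rooms, which puts that variation back.

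For the primary outcome, the possible consequence is a real effect missed by a test that is stricter than its nominal level. At sample-area level a second dependence arises: three samples come from one randomised side but would be counted as three independent observations. That pushes the error in the opposite direction.

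The protocol commits to a specific test that does not fit its own randomisation, so this is not a detail left open for a later analysis plan.

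**Working it through.** **1. Reproduce the plan's own figure.** Rooms 50, sides 2, locations 3, time points 2: 50 x 2 x 3 x 2 = 600, as stated. With one arm per room the count would be 50 x 3 x 2 = 300. The sample count therefore requires both arms in every room.

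**2. Side totals (50 against 50): type I error.** Assume log CFU with SD 1 on each side and left-right correlation r. The true variance of the arm difference is (1 - r) times what an independent-samples test assumes. The true two-sided error at nominal 5% is about 2 x [1 - Φ(1.96/√(1 - r))].

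- r = 0: 5.0%
- r = 0.3: 1.96/√0.7 = 2.34, giving 1.9%
- r = 0.5: 1.96/√0.5 = 2.77, giving 0.6%

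Simulated rank sum error agrees: 4.7%, about 2.0-2.3%, and 0.6-0.7%. The signed-rank test stays at 4.4-5.4%.

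**3. Side totals: power.** For a shift of d SD, the unpaired statistic is centred near d x √(50/2). At d = 0.4 this is 0.4 x 5 = 2.0, just above 1.96, which is why rank sum power stays near 50% whatever the correlation. The paired statistic is centred near 2.0/√(1 - r), which is 2.39 at r = 0.3 and 2.83 at r = 0.5. Simulated power for 50 pairs on the log scale (ranges span repeated runs):

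| Shift (assumed) | r (assumed) | Rank sum | Signed-rank |
|---|---|---|---|
| 0.4 SD | 0 | 51% | 50% |
| 0.4 SD | 0.3 | 47-51% | 60-65% |
| 0.4 SD | 0.5 | 47-49% | 75-78% |
| 0.6 SD | 0.3 | 87% | 93% |
| 0.6 SD | 0.5 | 90-91% | 98% |
| 0.8 SD | 0.3 | 99% | 100% |
| 0.8 SD | 0.5 | about 100% | about 100% |

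**4. Scale.** The rank sum test is unaffected by a log transform; the signed-rank test is not. On untransformed CFU (assumed SD of ln CFU = 2) at 0.4 SD, rank sum against signed-rank power is 48% v 40% at r = 0, 49% v 51% at r = 0.3 and 48% v 65% at r = 0.5.

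**5. Pooled sample areas (150 against 150).** Split the variance into a room share R, a side-within-room share S and the remainder. The room effect cancels in the arm difference. The side effect is shared by three samples and does not cancel. The ratio of true to assumed variance is 3S + (1 - R - S) = 1 + 2S - R.

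| R (assumed) | S (assumed) | Ratio | Simulated type I error |
|---|---|---|---|
| 0.3 | 0 | 0.7 | 2.0% |
| 0.3 | 0.1 | 0.9 | 4.1% |
| 0.3 | 0.2 | 1.1 | 6.1% |
| 0.1 | 0.2 | 1.3 | 8.5% |

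The test is conservative when R exceeds 2S and anti-conservative when it does not. More extreme shares widen the range: R = 0 with S = 0.3 (ratio 1.6) gave 11.9%.

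**The case against.** The case on the other side has real force about the consequences, but not about the mismatch itself.

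- **Direction.** A reader might infer that every CFU p-value will be too large. The document does not support that. It gives no left-right correlation, the side-total test loses nothing at zero correlation, and the pooled sample-area test can err the other way. Change from baseline already removes part of a stable room effect, so any loss for that secondary outcome may be smaller.
- **Size.** The 0.4 SD shift is an assumption. At 0.6 SD the gap is 6 to 8 points and at 0.8 SD it has almost gone, so a general claim that a real effect would probably be missed goes too far.
- **Validity.** For side totals under positive correlation the error lies below 5%, so a significant primary result would not be a false-positive artefact. The primary problem is lost efficiency.
- **The couplet lines.** Taken literally, a rank sum test inside one couplet could never reach 0.05: the smallest two-sided p is 1.0 for 1 v 1 and 2/20 = 0.10 for 3 v 3. That reading is strained. The list also contains items that are not tests, and the lines more naturally mean a pairwise comparison across all couplets. They suggest the pairing was recognised, but no paired test is attached to them.
- **Layout.** Some wording fits side randomisation poorly: application is described across the room, totals are called room totals, and the term couplet is kept. The two-room couplet design in the exemption application gives a room's partner the opposite arm, so the arms would be matched on that reading too.

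**Conclusion.** The point holds in a conditional form. The named test contradicts the matched design, and the protocol's own sample count confirms that design.

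For the primary side-total comparison, the harm depends on positive left-right correlation. Shared occupant and cleaning make that plausible, but no value is given. At assumed correlations of 0.3 to 0.5 the power lost is roughly 13 to 30 points for a 0.4 SD log shift, and little for larger effects.

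For pooled sample-area CFU, the error rate is not controlled at 5% in a known direction: about 2% to 8% under moderate assumed variance shares.

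The simulations use continuous normal log values without zeros or ties, so the figures show order of magnitude, not a forecast for this trial.

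**What to change.** 1. **Primary between-arm comparison.** Replace the rank sum test with a Wilcoxon signed-rank test on the 50 within-room differences (intervention side minus control side) in log10(CFU+1), or an equivalent paired model. Report an estimate and 95% CI. State the log scale explicitly, because changing only the test name gains little at low correlation.
2. **Sample-area CFU.** Use a paired test for each location, or a mixed model with room and side-within-room effects.
3. **Within-couplet comparisons.** Define these as the paired analysis across all rooms, not a test inside a single couplet.
4. **Wording.** Reconcile the passages on room-wide application, room totals and couplets with side-level randomisation.

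The cost is a short revision of the Analysis section, some cleaning-up of terms and slightly more analysis work. No further rooms, samples or data are needed. If the correlation is zero, the log-scale paired test gives up essentially no power (50% v 51% at 0.4 SD). The change should be made before any comparison by arm, so that the choice of test cannot depend on the result.
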